## Abstract

**Background:**

To achieve an adequate visual working field during laparoscopic colorectal surgery without disturbance of the small intestine, patients are positioned in the Trendelenburg position. This position results in hemodynamic changes that may increase the risk of cardiopulmonary complications and prolonged hospital stay. Recently, an intraoperative retractor sponge was introduced as an alternative to the Trendelenburg position during laparoscopic surgery.

The objective of this trial is to study the impact of the use of an intraoperative retractor sponge on the duration of the hospital stay and risk of perioperative complications in patients undergoing laparoscopic surgery for colorectal cancer.

**Methods/design:**

The SPONGE trial is a monocenter study and follows the cohort multiple randomized controlled trial (cmRCT) design. It will be conducted within a multicenter prospective observational cohort of colorectal cancer patients of all stages, for whom longitudinal clinical data and patient-reported outcomes are collected. Patients within the cohort, who will undergo laparoscopic surgery for distal colon or rectal cancer, are eligible for inclusion and form a subcohort. From this subcohort, a 1:1 random sample will be offered to undergo surgery with the use of the retractor sponge. Patients from the subcohort who are not selected will undergo standard treatment, that is, surgery in the Trendelenburg position. The primary endpoint is the duration of the postoperative hospital stay. Secondary outcomes are duration of surgery; intraoperative blood loss and fluid balance; and postoperative body temperature, oxygenation and complications. Both arms require 94 patients.

**Discussion:**

This study is the first randomized controlled trial to evaluate the effect of sponge-assisted laparoscopic colorectal surgery in comparison with standard Trendelenburg position on hospital stay and peri- and postoperative complications. Results of this study will also be relevant for other surgical procedures in the pelvic region. The present study is the second randomized controlled trial according to the cmRCT design, which is embedded within our colorectal cancer cohort.

**Trial registration number:**

ClinicalTrials.gov NCT02574013. Registered 27 September 2015.

## Background

Colorectal cancer is the fourth most common cause of cancer worldwide with the highest incidence in developed countries [1]. Surgery is still the cornerstone of curative colorectal cancer treatment. In the Netherlands, more than half of the colorectal resections is performed laparoscopically [2]. In laparoscopic colorectal surgery, a clear view on the operating field without disturbance of the small intestine in the pelvic region is essential. To achieve this, patients are positioned in a head down (Trendelenburg) position, having gravity retract the intestines away from the pelvic region to obtain a clear working field [3]. The Trendelenburg position is associated with hemodynamic instability due to the increased intrathoracic and intracranial pressure [4–6]. This may complicate anesthetic control and could potentially cause postoperative airway obstruction due to laryngeal edema, and a decrease in postoperative lung function [7–9]. Nevertheless, the effects of the Trendelenburg position on postoperative outcomes, for example, cardiac and pulmonary complications and hospital stay, are still unclear because alternatives for the Trendelenburg position have not been available so far.

Recently, the Endoractor™ (CE Kawamoto Corporation, Osaka, Japan) retractor sponge has been introduced to keep the small intestine aside and create a proper view during laparoscopic pelvic surgery while the patient is in a horizontal position. The initial Dutch experience with the retractor sponge comes from a nonrandomized matched pilot study in which 45 patients underwent sponge-assisted operations and 45 control patients were operated on while in the Trendelenburg position [10]. Patients who underwent sponge-assisted surgery had a shorter hospital stay compared to those in the Trendelenburg position (5.4 and 7 days, respectively, *P* = 0.041). Fewer cardiac complications were observed in the sponge-assisted surgery group compared to the Trendelenburg group, although this difference was not significant (one patient with heart failure versus three patients with heart failure and one patient with myocardial infarction, respectively). These results seem promising; however, confirmation with larger numbers in a randomized setting is required.

Herein, we present a trial designed to evaluate the effect of sponge-assisted laparoscopic colorectal surgery on the duration of hospital stay in comparison with standard care, that is, surgery in the Trendelenburg position. In addition, we will assess the impact of sponge-assisted surgery on postoperative complications, perioperative blood loss and fluid balance, operation time, and postoperative oxygenation and body temperature.

## Methods/design

### Study design

The SPONGE trial is a monocenter randomized controlled trial conducted within a multicenter observational prospective cohort of colorectal cancer patients. This project is launched as the prospective initiative colorectal cancer cohort (Dutch: “Prospectief Landelijk ColoRectaal carcinoom Cohort” (PLCRC)) and follows the protocol of the “ProspectIve data CollectioN Initiative on Colorectal cancer (PICNIC)” (ClinicalTrials.gov: NCT02070146). This cohort was initiated in 2012 at the University Medical Center Utrecht (the Netherlands) and includes colorectal cancer patients of all stages. The cohort follows the “cohort multiple Randomized Controlled Trial” (cmRCT) design, which aims to facilitate multiple pragmatic randomized controlled trials simultaneously [11].

### Cohort informed consent procedure

Patients are enrolled in the cohort after a diagnosis of colorectal cancer. Informed consent for the longitudinal collection of clinical data is required for inclusion. Additionally, patients may provide optional consents to fill-out questionnaires on patient-reported outcomes and for the collection of biomaterials (tumor tissue and blood sample). Upon enrollment, patients are also asked to provide “broad consent for randomization,” according to the staged-informed consent procedure developed for cmRCT [12]. This means that patients may be randomly selected for experimental interventions in the future if eligible for this intervention. These patients will then be offered this experimental intervention, which they may accept or refuse. In case of refusal, patients receive standard care. Only patients who accept the offer will sign an additional informed consent. Patients who are eligible for the experimental intervention but who are not randomly selected will undergo standard care and will not be informed about the experimental intervention. They will serve as controls and their data are compared to the randomly selected patients who were offered the intervention.

### Patient recruitment

For the present study, patients are enrolled in the cohort at the Department of Surgery of the St. Antonius Hospital, Nieuwegein, The Netherlands. Eligible patients meet the following inclusion criteria: 1) histologically confirmed distal colon (sigmoid) or rectal cancer, 2) planned for elective laparoscopic colorectal surgery, 3) performance status WHO 0 to 2 [13], and 4) broad consent for randomization (Table 1). Patients with an indication for open colorectal surgery or emergency colorectal surgery and patients with an inadequate understanding of the Dutch language in speech and/or writing are excluded.

**Table 1 Tab1:** Inclusion and exclusion criteria for the SPONGE trial

Inclusion criteria	Exclusion criteria
Participant in the PLCRC project	Indication for open colorectal surgery
Informed consent obtained for being offered experimental interventions within the PLCRC project	Emergency colorectal surgery
Distal colon (sigmoid) or rectum carcinoma	Inadequate understanding of the Dutch language in speech and/or writing
Elective laparoscopic surgery	
Performance status WHO 0 to 2	

PLCRC, prospective cohort of colorectal cancer patients; WHO, World Health Organization performance status

### Random selection

Participants who meet the inclusion criteria of the SPONGE trial form a subcohort of eligible patients (Fig. 1). From this subcohort, patients are randomly selected on a 1:1 basis. Randomly selected patients are offered sponge-assisted surgery. Stratified randomization is performed to take into account participation in other ongoing trials within the cohort, of which the (secondary) endpoints may interfere with endpoints of the SPONGE trial. At this moment, patients are stratified according to whether they received boost radiotherapy in the context of the RECTAL BOOST study, which is running as a cmRCT within the cohort (ClinicalTrials.gov: NCT01951521) [14]. In this trial, a randomly selected group of patients with locally advanced rectal cancer is offered an additional radiation boost prior to standard neoadjuvant chemoradiation. Stratified randomization, using dedicated software, takes place at the Imaging Division University Medical Center Utrecht.

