This trial is relevant because the number of (non-)surgical postoperative complications after colorectal surgery is substantial and result in a relatively high morbidity and mortality rate [19, 20]. Even though laparoscopic colorectal surgery is associated with certain benefits as a shorter hospital stay, less blood loss, and a faster recovery of bowel function, the risk on postoperative cardiopulmonary complications is not evidently lower than in open surgical procedure. A systematic review on nonsurgical complications following laparoscopic or open surgery for colorectal cancer showed no difference in the risk of pulmonary complications (pooled analysis for laparoscopy in colon cancer (OR 0.78, 95 % CI 0.53 to 1.13) and in rectal cancer (OR 1.19, 95 % CI 0.74 to 1.90)) [21]. Significantly fewer cardiac adverse events were observed in patients undergoing colectomy, but not in those undergoing rectal surgery (OR 0.28, 95 % CI 0.11 to 0.71 and OR 0.85, 95 % CI 0.41 to 1.71, respectively). This could be a result of the more extensive surgery, longer operation time, and higher risk on overall postoperative morbidity in rectal surgery [22]. Several studies presented the effects of the Trendelenburg position on perioperative cardiopulmonary parameters, but postoperative data are lacking [7, 8, 23–26]. Besides, the effect of a patient’s position as an independent factor is hard to evaluate because the perioperative hemodynamic parameters are partly influenced by pneumoperitoneum, which is the CO_2_ gas insufflation in the abdominal cavity [3].

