A challenging aspect of the cmRCT design is the fact that multiple trials are conducted simultaneously within one cohort. In patients eligible for multiple trials, interference of endpoints between trials might occur. As mentioned earlier, some of the patients eligible for the SPONGE trial will have participated in the RECTAL BOOST study [14]. Patients having received the boost intervention potentially have a higher risk on acute toxicity than patients who undergo standard chemoradiation [30], which could result in perioperative complications and thereby prolonged hospital stay. In order to balance the number of patients treated with the experimental boost intervention between both arms, stratified randomization is required. The main advantage of stratified randomization is the systematic balance of factors, which may influence outcome measures between treatment groups resulting in trial efficiency, increased power and less need for (biased) post-hoc analysis [31]. Furthermore, stratified randomization enables the possibility to detect potential interactions between the boost intervention and outcome measures of the SPONGE trial. On the other hand, the more trials conducted within one cohort, the more strata required for randomization in every new trial. This will result in complex trial coordination, treatment allocation, and trial administration. Having too much trial-induced strata may result in overstratification. This could lead to unfilled strata, unequal distribution of stratification factors, or the need for adjusted analysis [31–33]. In addition, it is yet unclear if there is such as a limit in number of interventions per patient within the cmRCT design. In our cohort, these new methodological challenges should be taken into account when a new trial is initiated. In the future, expertise of clinicians will be essential in the design of new cmRCT-based trials because overlap of endpoints must be considered in an early stage since this could affect potential recruitment rates and thereby the succeeding of a trial.

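### Tumour site is left to chance at randomisation and adjusted for only if imbalance appears, which costs precision without causing bias

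*Protocol article*

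**What the plan says.** Patient recruitment in the protocol article admits patients with "histologically confirmed distal colon (sigmoid) or rectal cancer", so two tumour sites are pooled.

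Random selection names one stratification factor: "At this moment, patients are stratified according to whether they received boost radiotherapy in the context of the RECTAL BOOST study". It also gives the reason: "Stratified randomization is performed to take into account participation in other ongoing trials within the cohort". In the boost trial, "a randomly selected group of patients with locally advanced rectal cancer is offered an additional radiation boost", so no sigmoid patient can be in the boost stratum.

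The Discussion comments on a review in which the cardiac benefit of laparoscopy appeared in colon but not in rectal surgery: "This could be a result of the more extensive surgery, longer operation time, and higher risk on overall postoperative morbidity in rectal surgery". Later it states what stratifying is for: "The main advantage of stratified randomization is the systematic balance of factors, which may influence outcome measures between treatment groups". It also warns that "Having too much trial-induced strata may result in overstratification".

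Statistical analysis names t-tests or nonparametric equivalents for continuous outcomes, and chi-squared or Fisher's exact tests for categorical ones. Adjusted analyses follow only if randomisation proves unbalanced; the article gives no criterion for imbalance and no covariates. Data collection lists tumour characteristics, neoadjuvant therapy and surgical procedure among the baseline items. Blinding states that the trial is not blinded.

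**The concern.** The stratum without boost holds every sigmoid patient and every rectal patient who did not receive the boost. Nothing balances the arms on tumour site within it.

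The features the Discussion attributes to rectal surgery bear on the trial's endpoints. Duration of surgery and complications are secondary endpoints. The discharge checklist requires that no active, untreated complication is present, so morbidity feeds into the primary endpoint, stay. The Discussion's argument for the boost stratum (a factor that may cause complications and so prolong stay) applies to tumour site as well.

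The analysis does not recover what randomisation leaves open. The named tests use no covariate. The adjustment rule depends on what is observed, in a trial where treatment is known, so whether and how to adjust can be decided after seeing the arms. At stake are the precision of the primary comparison and the credibility of any later adjustment.

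**Working it through.** **Inputs from the protocol article (Sample size, Abstract).** Two-sided 5% test; 80% power; SD 2.04 days; target difference 1 day; 10% refusal; 82 per arm before the 15% nonparametric allowance. The final size is 94 per arm in the Abstract and 98 in Methods. That conflict is a separate matter; both values are used here.

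**Assumed, because the documents do not give them.** Rectal share p = 30% to 50%; sigmoid–rectal difference in mean stay g = 1 to 2 days. The SD of 2.04 is taken to include the between-site variance.

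**Step 1: the plan's own figure.** n per arm = 2 × (1.96 + 0.842)² × 2.04² / 1² = 65.3, so 66. If refusal dilutes the effect to 0.9 day, 65.3 / 0.81 = 80.7, so 81 by the normal formula; the noncentral t gives 82. The plan's 82 reproduces. Adding 15% gives 82 × 1.15 = 94.3.

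**Step 2: chance imbalance in rectal share.** SD = √(2p(1−p)/n).
- n = 94: 0.0668 (p = 0.3) and 0.0729 (p = 0.5). Times 1.96: ±13.1 and ±14.3 percentage points.
- n = 98: 0.0655 and 0.0714. Times 1.96: ±12.8 and ±14.0 points.
- The probability of a gap above 10 points is 13% to 17% across these cases.

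These ranges treat tumour site as wholly unstratified. The boost stratum is all rectal, so the true range is somewhat narrower if many patients received the boost.

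**Step 3: shift in the treatment difference, variance share and power.** Shift = 1.96 × SD × g. Variance share = p(1−p)g²/2.04². Power is for 0.9 day at 82 per arm (the size before the 15% allowance), first with SD 2.04 and then with the site variance removed.

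| p | g (days) | 95% shift, n = 94 | 95% shift, n = 98 | Variance share | Power with site used |
|---|---|---|---|---|---|
| 0.3 | 1 | ±0.13 | ±0.13 | 5% | 0.83 |
| 0.5 | 1 | ±0.14 | ±0.14 | 6% | 0.83 |
| 0.3 | 2 | ±0.26 | ±0.26 | 20% | 0.89 |
| 0.5 | 2 | ±0.29 | ±0.28 | 24% | 0.90 |

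Power without site is 0.81. Expressed as sample size, the 81 per arm of Step 1 falls to 76–77 (g = 1) or 62–65 (g = 2).

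**Step 4: is the shift additional to the standard error?** At n = 94 the unadjusted standard error is 2.04 × √(2/94) = 0.298 day (95% ±0.58). For p = 0.5 and g = 2, the within-site SD is √(2.04² − 0.25 × 4) = 1.778, with standard error 1.778 × √(2/94) = 0.259. The site part is 0.0729 × 2 = 0.146. Combined, √(0.259² + 0.146²) = 0.298. The site shift is a component of the planned standard error, not an addition to it.

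**The case against.** The strongest reply is that the protocol already has a safeguard: it promises adjusted analyses when randomisation is unbalanced and collects the tumour data needed. Naming covariates is commonly left to an analysis plan that is not shown. This stands as far as the missing covariate list goes, and that list is not the complaint. The conditional rule itself is fixed in the article, and it makes adjustment depend on the data. The Discussion counts less need for biased post-hoc analysis among the benefits of stratifying, so leaning on such a rule sits badly with its own reasoning.

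Second, boost is a legitimate factor. The Discussion explains that boost toxicity could lead to complications and longer stay, and stratification was introduced to handle overlap with other cohort trials. This stands. A reader might infer that the wrong factor was balanced, or that the protocol contradicts itself. Neither follows: describing an advantage of stratification is no commitment to stratify on every prognostic factor.

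Third, a reader might take tumour site to be the main prognostic factor. No section ranks prognostic factors or reports stay by site. The remark on rectal surgery is tentative, compares it with colon surgery in general rather than sigmoid resection, and does not mention stay.

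Fourth, more strata could bring overstratification. That warning concerns strata created by accumulating cohort trials. Because boost occurs only in rectal patients, adding tumour site gives three levels instead of two.

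**Conclusion.** The concern holds as a loss of precision that can be avoided at no cost in patients. It is not a bias: chance imbalance on tumour site is covered by the standard error, type I error is controlled, and the unadjusted comparison still meets its 80% target at about 0.81.

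Under the assumed rectal share of 30% to 50% and site difference of 1 to 2 days, the 95% chance shift is about ±0.13 to ±0.29 day, and always using tumour site would lift power to between 0.83 and 0.90. If the site difference is well below 1 day, the gain is negligible.

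A reader might infer that a chance excess of rectal operations could mimic or hide the 1-day effect. The figures do not support that. Even a 3-day site difference gives only about ±0.43 day (0.143 × 3), and tumour site would then account for 45% to 54% of the planned variance. A full 1-day shift would need a 33-point imbalance at a 3-day difference (about 4.6 SD) or a 50-point imbalance at 2 days (about 6.9 SD).

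**What to change.** In Statistical analysis, replace the conditional adjustment rule. The primary comparison of stay should always account for a prespecified three-level factor (sigmoid; rectum without boost; rectum with boost), whatever imbalance is observed. A stratified rank test or a regression model would serve; choose one before the outcome data are examined. The factor can be built from tumour data already collected and from boost status, so it also covers patients already selected.

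Optionally, use the same three levels to stratify the remaining randomisations. Tumour site is an eligibility item and so is known before selection. This changes allocation while the trial is enrolling, and most of the gain comes from the analysis, so it is not essential.

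Cost: an amendment to the analysis text and, if the option is taken, one more level in the randomisation software; no extra patients or data. Limits: the boost level may hold few patients, so state in advance how a level represented in only one arm is handled. Patients already selected were not balanced on tumour site. Rectal patients without boost would still differ in neoadjuvant treatment.

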**Fig. 1 Fig1:**
[figure not shown]
Overview study design and treatment allocation. PLCRC, prospective cohort of colorectal cancer patients; SPONGE trial, randomized controlled trial for clinical evaluation of an intraoperative retractor SPONGE in laparoscopic colorectal surgery

### Study specific informed consent procedure

Patients randomly selected to be offered the sponge-assisted surgery form the intervention group. If these patients accept the offer, additional informed consent is signed to undergo sponge-assisted surgery. Patients who are eligible but who are not randomly selected form the control group and undergo standard treatment, that is, surgery in Trendelenburg position. According to the cmRCT design, patients in the control group will not be informed about the sponge-assisted surgery intervention and will not sign additional informed consent.

### Blinding

This trial is not blinded. The cmRCT design does not enable blinding of participants in the intervention arm. Randomly selected patients will be informed about the sponge intervention and must accept or refuse the sponge-assisted surgery. Patients in the control group are blinded to the fact that they serve as controls in the SPONGE trial. Investigators and physicians cannot be blinded to sponge use because operation reports require indication of the used devices for safety reasons.

### Intervention

The intervention group consists of all patients that have been randomly selected to receive an offer for sponge-assisted surgery. The sponge will be used only in patients who have accepted the intervention. The sponge, the Endoractor™, is a sterile device made of compressed cellulose material, which makes it suitable to fit through a 12-mm port. When inserted into the abdominal cavity, saline increases the sponge size approximately nine times and retracts organs by displacement, weight, and friction. First, the patient is positioned in the Trendelenburg to allow sponge positioning. After placement, the patient is repositioned into a horizontal position. After completion of the surgery, the sponge can be removed easily through a 12 mm port incision.

No side effects or complications related to sponge use were reported in a previous study [15] or in the pilot study. The sponge was tested for potential adverse effects such as cytotoxicity and intracutaneous reactivity [15]. No tissue trauma or organ damage due to the sponge has been reported so far. The retractor sponge is X-ray detectable in case it was left inside the abdomen. The center in which the study is performed handles a strict surgical safety checklist, which includes noting sponge use, making the chance highly negligible that the sponge will not be removed from the abdomen. Presently, the SPONGE trial is being conducted with an experienced colorectal surgeon who has been working with the retractor sponge since 2013. In the near future, other colorectal surgeons will participate. Before participating in the study, surgeons will have completed a learning curve of 10 sponge-assisted surgeries.

